##### Apolipoprotein E4

The status of Apolipoprotein Epsilon 4 (ApoE4) is determined as a baseline variable and is taken from two buccal mucosa swabs (Catch-All swabs of the firm BIOzymTC example). ApoE4 might modify the effects of pharmacological treatments. An ApoE4 carrier may react different on a certain treatment, e.g. cholinesterase inhibitors [40]. To control for a possible influence of ApoE4 on treatment effects, we analyze ApoE4.

### Instruments caregivers

#### Primary outcome measure

##### Depressive symptoms

To measure depressive symptoms the self-rating 20-item report scale Centre for Epidemiologic Studies-Depression (CES-D; [41,42]) is used.

Higher scores indicate more severe depressive symptoms.

#### Secondary outcome measures

##### General health

One self-report question on general health is used. A higher score indicate higher impairment.

##### Burden

The Self-Perceived Pressure from Informal Care (SPPIC); [43,44] is applied to measure caregivers' feelings of role overload. Higher scores indicate more perceived pressure/feelings of role overload.

To assess caregiver distress the Revised Memory and Behaviour Problem Checklist (RMBPC) [28,29] is used. This is a 24-item caregiver-report measure of observable behavioural problems in people with dementia in relation to caregiver distress. Higher scores indicate higher caregiver distress.

##### Adrenocortical activity

Salivary cortisol is analyzed to measure adrenocortical activity. Several studies showed that salivary cortisol is a reliable reflection of cortisol levels in blood [45]. Cortisol is assessed by sampling saliva at the time of awakening and within the first 30 min after awakening. Early morning cortisol levels seems to be a biological marker for the individual's adrenocortical activity when measured with strict reference to the time of awakening [46].

#### Measurement of possible confounders

To collect dyads' demographic information and information about their health status questions are asked concerning nationality, birth date, living situation, education, ethic origin, use of medication, history of mental and physical health, present health status, Body Mass Index, use of alcohol and drugs, exercise history, dementia type, patient-caregiver relationship and care service use.

#### Statistical analysis

Data will be analyzed according to the intention-to-treat principle. Outcome analyses will compare the intervention group with the comparison group using regression analysis [47]. Baseline differences in demographic and clinical characteristics will be investigated using Chi-square tests, *t*-tests, and analysis of variance (ANOVA).

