**Methods/Design:**

This manuscript describes the design of a Randomised Controlled Trial (RCT) of the effects of a home-based exercise and support programme for people with dementia and their caregivers. The aim is to randomly assign 156 dyads (caregiver and dementia diagnosed person) to an intervention group or a comparison group. The experimental group receives a home programme in which exercise and support for the people with dementia and their caregivers are combined and integrated. The comparison group receives a minimal intervention. Primary outcomes are physical health (people with dementia) and mood (people with dementia and caregivers). In addition, to get more insight in the working components of the intervention and the impact of the intervention on the relationship of the dyads a qualitative sub-study is carried out.

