### Sample size/Power

Sample sizes were calculated by a statistical power analysis. To detect an effect size of *d *> 0.40 between the two conditions with α = .05 and β = .80, 78 dyads in each group are needed.

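### The 156 dyads to be randomised are exactly the 2 × 78 needed with complete outcomes, leaving no allowance for loss, and 78 per group gives 80% power only for an unstated one-sided test

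*Protocol article*

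**What the plan says.** - **Protocol article, Sample size/Power:** the effect size is d above 0.40, and the calculation is given as "between the two conditions with α = .05 and β = .80, 78 dyads in each group are needed". The section does not say whether the test is one- or two-sided. It gives no drop-out rate and no baseline correlation.
- **Protocol article, Abstract (Methods/Design):** "The aim is to randomly assign 156 dyads", split between two groups.
- **Protocol article, Measurements:** both groups are assessed at baseline, 3 months and 6 months. Only the intervention group is assessed at 12 months.
- **Protocol article, Statistical analysis:** "Data will be analyzed according to the intention-to-treat principle". The groups are to be compared by regression. Covariates, the use of repeated measures and the handling of missing outcomes are not described.

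**The concern.** A number that is needed for the analysis has been used, unchanged, as the number to randomise. That is harmless only if every dyad supplies its outcomes at 3 and 6 months or if the calculation has slack.

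Some loss is foreseeable. The participants are people with dementia and caregivers who already report some depressive symptoms. Both members of the dyad have primary outcomes. The SF-36 and SIP for the person with dementia are completed by the caregiver, and the Cornell scale is completed with the caregiver, so losing the caregiver also loses outcomes of the person with dementia.

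What is at stake is how a null result is read. If the true power for d = 0.40 is nearer 60 to 75% than 80%, a non-significant difference says less about the absence of such an effect than the protocol suggests.

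**Working it through.** **Inputs.** From Sample size/Power: d = 0.40 (SD taken as 1), α = 0.05, 78 per group. The printed β of .80 is read as power of 0.80; a literal β of 0.80 would need only 16 per group two-sided or 9 one-sided. From the abstract: 156 randomised, and 156 / 2 = 78. Loss rates and baseline correlations are my assumptions, because the article gives neither.

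**Step 1: reproduce the 78.** By the normal approximation, n per group = 2(z_α + z_0.80)² / d².
- One-sided: 2(1.645 + 0.842)² / 0.16 = 77.3, so 78. The noncentral t gives 77.97, so also 78.
- Two-sided: 2(1.960 + 0.842)² / 0.16 = 98.1, so 99. The noncentral t gives 100.

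The printed figure matches the one-sided test exactly and does not match the two-sided test.

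**Step 2: power at 78 with no loss (noncentral t).** The noncentrality is d√(n/2) = 0.40 × √39 = 2.498 on 154 degrees of freedom. The critical values are 1.655 one-sided and 1.975 two-sided.
- One-sided: 80.0%. At 77 per group it is already 79.6%, so there is no slack.
- Two-sided: 69.9%.

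**Step 3: power after loss.** The same formula with n = 78 × (1 − loss), unadjusted, d = 0.40:

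| Assumed loss | Evaluable per arm | One-sided | Two-sided |
|---|---|---|---|
| 0% | 78 | 80.0% | 69.9% |
| 10% | 70.2 | 76.2% | 65.3% |
| 15% | 66.3 | 74.1% | 62.8% |
| 20% | 62.4 | 71.8% | 60.1% |
| 25% | 58.5 | 69.3% | 57.4% |

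Drop-out alone costs 80.0 − 76.2 = 3.8 to 80.0 − 69.3 = 10.7 points one-sided, and 69.9 − 65.3 = 4.6 to 69.9 − 57.4 = 12.5 points two-sided. The other 80.0 − 69.9 = 10.1 points of the two-sided shortfall come from the sidedness, not from loss.

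**Step 4: what an allowance would have required.** On the one-sided reading, 78 / (1 − loss) for 10, 15, 20 and 25% loss is 87, 92, 98 and 104 per group.

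**Step 5: effect of baseline adjustment.** With baseline correlation r, the residual SD is √(1 − r²), so d becomes 0.40 / √(1 − r²). At r = 0.6 this is 0.40 / 0.8 = 0.50. With 15% loss the noncentrality is 0.50 × √(66.3 / 2) = 2.88, and two-sided power is 81.5%. At the same loss, r = 0.5 gives 75% and r = 0.7 gives 89%. (The degree of freedom used by the covariate is ignored; its effect is negligible.) By the normal approximation, 80% power two-sided needs 74, 63 and 51 per group at r = 0.5, 0.6 and 0.7, so 78 tolerates about 5%, 19% and 35% loss.

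**The case against.** The strongest reply is that the planned analysis is a regression and baseline scores are collected. An adjusted model could keep 80% power despite moderate loss, as Step 5 shows. A reader might go further than this point does and infer that the stated power fails however the analysis is done. The documents do not support that, because at r = 0.6 the two-sided test survives about 19% loss. What stands is that the sample-size statement cites no correlation and claims no such gain, while its figure coincides with the unadjusted one-sided calculation. The possible gain therefore does not support the printed figure as written.

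A reader might also infer that the analysis contradicts its intention-to-treat promise, since an ordinary regression at one visit omits dyads without that visit's outcome. The article names only regression. It plans no completer analysis and no separate model per visit, and rules for missing outcomes may sit in the full protocol or SAP, which are not shown. That is no finding.

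A third inference is that loss will be greater in the intervention arm, because pilot caregivers found the sessions too many and too frequent. The section on the intervention group reports the response in the same place: sessions were cut from 12 to 8, and the first-month frequency from two per week to one. No attrition figure is given for either arm, so unequal loss is conjecture.

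Finally, the effect of drop-out can be overstated. On the one-sided reading a 5% loss costs under 2 points, and the low two-sided figures owe much to the sidedness.

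**Conclusion.** The concern holds as a sample-size point. The randomisation target equals the complete-outcome requirement. On the calculation's own unadjusted terms, any loss takes power below 80%, whichever sidedness is meant. The loss of power from drop-out is modest to moderate: about 4 to 11 points one-sided, or about 5 to 13 points two-sided, for 10 to 25% loss. If the test is two-sided, power starts at 69.9% instead of 80%.

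These sizes rest on d = 0.40, equal loss in the two arms, no baseline adjustment and assumed loss rates. They do not show that the trial is underpowered under every analysis, and they show no departure from intention-to-treat. The stated power should be corrected because it is a figure on which the trial's conclusions will lean.

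**What to change.** Keep 156 dyads and amend two sections.

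1. **Sample size/Power:** state whether α = 0.05 is one- or two-sided, and print 0.80 as power instead of β. Give an expected loss, and restate power at the expected evaluable number per arm (for example about 66 at 15% loss) instead of at 78.
2. **Statistical analysis:** specify that the regression adjusts for the T0 value of the outcome, which is already collected. State the baseline correlation assumed in the power statement and show a range. For example, r = 0.6 with 15% loss gives about 82% two-sided, but r = 0.5 gives only 75%.

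Optionally, model T1 and T2 jointly by a likelihood-based method that uses every randomised dyad with at least one post-baseline outcome. This serves the intention-to-treat aim.

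The cost is wording in two sections and slightly more analysis work, with no added recruitment. The stated power may become less favourable. If the expected loss or correlation does not support 80%, the protocol should say so.

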### Qualitative sub study

The qualitative part of this study provides more insight into the working components of the home-based intervention as perceived by the people with dementia and their caregivers. In addition, this qualitative study provides more insight into the impact of the intervention on the relationship of the dyads

## Methods

Semi-structured interviews are held with caregivers and people with dementia randomised to the intervention group. Consenting caregivers and people with dementia are individually interviewed at home. Caregivers and people with dementia with diverse sociodemographic characteristics are recruited. Recruitment continues until theoretical saturation is reached.

### Analysis

Interviews are audio taped and transcribed. The transcripts are initially coded using open codes based on the words the participants used. Coding starts after the first interview so that any emergent themes can be incorporated into subsequent interviews. The coding process is supported by ATLAS.ti (version 6.2; ATLAS.ti GmbH, Berlin, Germany). To ensure external validation and increase reliability, two researchers independently code the data. Differences are discussed until consensus is reached.

### Ethical principles

The study is conducted according to the principles of the Declaration of Helsinki and in accordance with the Medical Research Involving Human Subjects Act. The Medical Ethics Committee of the VU University Medical Center approved the study protocol (registration number 2008/320).

## Discussion

This paper describes the study protocol of a randomised controlled trial of a home-based physical exercise and support programme for people with dementia and their caregivers. Home-based psychosocial interventions for people with dementia and their caregivers are highly relevant, because in the coming years the number of people with dementia will increase and most of them will continue to live at home. Therefore, this study is aimed at the development of an evidence-based treatment of people with dementia and their caregivers in the community. Furthermore, a qualitative sub study is carried out to provide insight into the working components of the intervention as perceived by the people with dementia and the caregivers and to provide insight into the impact of this intervention on the quality of the relationship of the dyads.

A major strength of this study is the focus on both people with dementia and their caregivers. Both caregivers and people with dementia are included in the intervention and the potential outcomes of the intervention on both parties are assessed. We expect that both parties benefit from the intervention, both directly but also indirectly due to the positive effects on their counterpart. Another strength is the measurement of depressive symptoms from different perspectives with subjective and more objective measures to create a complete overview of mood in the dyads. Depressive symptoms of people with dementia are measured by clients' self-report (GDS-15) and caregivers' and clinical examiners' observation (Cornell and MDS-DRS RAI HC respectively). In addition, depressive symptoms of caregivers are measured by a self-report measure (CES-D) as well as by a biological marker (adrenocortical activity).

Designing a psychosocial intervention study also faces a number of challenges. First, it is impossible to blind coaches and the dyads for treatment conditions. The students that collect the data will be blinded to try to minimize the information bias effect. However, a risk is that the dyads disclose their group allocation during the assessments. Therefore, before each assessment dyads are asked not to inform the examiners about the intervention. To monitor the success or failure of the blinding, after each measurement the examiners are asked whether they know to which group the dyads had been allocated. Furthermore, the most appropriate control condition for this type of intervention could be debated. In this study, we chose to provide a minimal, but meaningful intervention to participants in the comparison group, rather than attention only. The minimal intervention consisted of written educational material and brief telephone calls.

This community-based intervention has the potential to improve the mental health of both people with dementia and their caregivers, which is highly relevant regarding the rising burden of dementia on society.
